## Abstract

**Background:**

Noninvasive respiratory support is frequently needed for patients with acute hypoxemic respiratory failure due to coronavirus disease 19 (COVID-19). Helmet noninvasive ventilation has multiple advantages over other oxygen support modalities but data about effectiveness are limited.

**Methods:**

In this multicenter randomized trial of helmet noninvasive ventilation for COVID-19 patients, 320 adult ICU patients (aged ≥14 years or as per local standards) with suspected or confirmed COVID-19 and acute hypoxemic respiratory failure (ratio of arterial oxygen partial pressure to fraction of inspired oxygen < 200 despite supplemental oxygen with a partial/non-rebreathing mask at a flow rate of 10 L/min or higher) will be randomized to helmet noninvasive ventilation with usual care or usual care alone, which may include mask noninvasive ventilation, high-flow nasal oxygen, or standard oxygen therapy. The primary outcome is death from any cause within 28 days after randomization. The trial has 80% power to detect a 15% absolute risk reduction in 28-day mortality from 40 to 25%. The primary outcome will be compared between the helmet and usual care group in the intention-to-treat using the chi-square test. Results will be reported as relative risk  and 95% confidence interval. The first patient was enrolled on February 8, 2021. As of August 1, 2021, 252 patients have been enrolled from 7 centers in Saudi Arabia and Kuwait.

**Discussion:**

We developed a detailed statistical analysis plan to guide the analysis of the Helmet-COVID trial, which is expected to conclude enrollment in November 2021.

**Trial registration:**

ClinicalTrials.govNCT04477668. Registered on July 20, 2020

**Supplementary Information:**

The online version contains supplementary material available at 10.1186/s13063-021-05988-x.

## Background

Acute hypoxemic respiratory failure is a common feature of severe coronavirus disease 19 (COVID-19) [1] and frequently requires respiratory support. As invasive mechanical ventilation carries high morbidity and mortality, other respiratory modalities, such as high-flow nasal oxygen (HFNO) and noninvasive ventilation (NIV) delivered via face mask or helmet, have been suggested and increasingly practiced. Helmet NIV has multiple advantages over other modalities that may include more effective seal, less transmission of the virus, more effective delivery of positive end-expiratory pressure (PEEP), and greater tolerance [2, 3]. Helmet NIV has been investigated as a treatment in adult patients with acute hypoxemic respiratory failure [4–8]. A network meta-analysis of 25 studies that included 3804 patients with acute hypoxemic respiratory failure for reasons other than COVID-19 found significantly lower risks of intubation (risk ratio, 0.26; 95% credible interval, 0.14–0.46) and mortality (risk ratio, 0.40; 95% credible interval, 0.24–0.63) with helmet NIV compared with standard oxygen therapy [9]. Recently, a randomized controlled trial (RCT) compared the early application of 48 h of helmet NIV to high-flow nasal oxygen (HFNO) in 109 patients with moderate to severe hypoxemia (ratio of partial pressure of arterial oxygen to fraction of inspired oxygen (PaO_2_:FiO_2_) ratio ≤ 200) and showed no difference in the number of days free of respiratory support at 28 days (primary outcome) with a significantly lower incidence of intubation and a higher number of invasive mechanical ventilation-free days at 28 days in the helmet NIV group [10].

The helmet noninvasive ventilation for COVID-19 patients (Helmet-COVID) trial is a concealed, unblinded multicenter RCT that evaluates the effect of helmet NIV plus usual care compared to usual care alone on 28-day mortality in patients with acute hypoxic respiratory failure due to COVID-19. The full trial protocol has been published previously [11].

In this manuscript, we describe the statistical analysis plan (SAP) of the Helmet-COVID trial. The report describes the procedures for the primary and secondary analyses. All analyses were prospectively defined as the SAP was finalized during trial implementation. The SAP was written by the principal investigator and members of the Steering Committee, who will remain blinded to the study results until all patients have been recruited and the database has been locked. Participant recruitment is expected to be completed in November 2021. The final study report will follow the CONSORT (Consolidated Standards of Reporting Trials) 2010 guidelines for reporting RCTs [12, 13].

## Methods

### Study design

The Helmet-COVID trial will enroll 320 critically ill patients in Saudi Arabia and Kuwait. The study has been approved by the Institutional Review Boards of the participating sites. The trial is registered in ClinicalTrials.gov (NCT04477668). The study is sponsored and funded by King Abdullah International Medical Research Center (protocol number RC20/306/R), Riyadh, Saudi Arabia. The sponsor has no role in the study design, management, or analysis.

### Study population

All adult (adult ICU cut-off age) patients admitted to the ICU with suspected or confirmed COVID-19 by reverse transcription-polymerase chain reaction (RT-PCR) will be screened for eligibility. Inclusion criteria include acute hypoxemic respiratory failure (PaO_2_:FiO_2_ ratio < 200 despite supplemental oxygen with a partial/non-rebreathing mask at a flow rate of 10 L/min or above) with intact airway protective gag reflex and ability to follow instructions. Exclusion criteria include imminent intubation and the requirement for more than one vasopressor. A full list of inclusion and exclusion criteria is described in the published protocol [11]. Enrolled patients will be randomized using a concealed online system to helmet NIV with usual care or usual care alone at a 1:1 ratio. Usual care may include mask NIV, HFNO, or standard oxygen therapy. Randomization will be stratified by site. Helmet NIV will be delivered in pressure support mode, with initial settings of pressure support of 8–10 cm H_2_O, PEEP of 10 cm H_2_O with FiO_2_ of 100%, targeting flow rate of ≥ 50 L/min with an inspiratory rise time of 50 ms, and end flow/cycling off of 50% of maximal inspiratory flow. The settings can be adjusted according to the study protocol. The management of respiratory support in the usual care group including mask NIV is at the discretion of the treating team.

A flow diagram will be constructed according to the CONSORT guidelines (Fig. 1). We will report the number of patients who were screened, met inclusion or exclusion criteria, and were eligible but not enrolled with reasons for non-enrollment. We will report the number of patients who were randomized to each group, received the allocated intervention, withdrawn/lost-to-follow-up with reasons, and included in the final analysis.

**Fig. 1 Fig1:**
[figure not shown]
CONSORT flow diagram

*The intention-to-treat population* consists of all randomized patients and will be used for the primary analysis. All randomized patients will be included regardless of whether they receive or do not receive the allocated intervention. All patients randomized with suspected COVID-19 will remain in the study, even if they tested negative for COVID-19 after enrollment. Post-enrollment exclusion from the intention-to-treat analysis will be restricted to the withdrawal of consent to use trial data by the patient or surrogate decision-maker (SDM) or wrong randomization (for example, randomization of an ineligible patient in error). However, if the patient or SDM withdraws consent for trial participation but permits collection and use of data, the patient will be included in the intention-to-treat analysis. We plan to enroll additional patients to compensate for patients who are excluded post-randomization, so the sample size of 320 patients in the intention-to-treat cohort is reached.

*The per-protocol population* consists of all randomized patients who receive respiratory support as per the allocated group (helmet NIV in the helmet NIV group, and no helmet NIV in the usual care group). Patients will be considered to have received helmet NIV if the device was applied for 1 h or more.

### Data

#### Baseline characteristics

We will present baseline characteristics in patients randomized to the helmet NIV and usual care groups in the intention-to-treat cohort (Supplement Table S1). We will report in the two groups patients’ age, sex, height, weight, body mass index, location before ICU admission (emergency room, hospital ward, other hospitals (ICU or ward), others), Acute Physiology and Chronic Health Evaluation (APACHE) II, Sequential Organ Failure Assessment (SOFA) score, comorbidities (any chronic comorbidity, chronic cardiac, pulmonary disease, renal, liver, and neurological diseases, diabetes, any malignancy including leukemia or lymphoma and metastatic solid tumor, AIDS/HIV, rheumatologic diseases, others). Because we are enrolling patients with confirmed or suspected COVID-19, we will report whether the patient is eventually confirmed to have COVID-19. We will report physiologic parameters before randomization (PaO_2_:FiO_2_ ratio, partial pressure of carbon dioxide (PaCO_2_), and pH) and the number of quadrants with infiltrates on the chest radiograph. We will report respiratory support at baseline (HFNO, mask NIV, standard oxygen therapy). We will document respiratory rate and whether the patient is treated with awake prone positioning. We will document the number of days from the onset of symptoms to the emergency room and ICU admission and the number of days from ICU admission to randomization. We will report non-respiratory organ support, including vasopressor therapy and renal replacement therapy.

#### Intervention data

For each 24 h in the first 96 h, we will report in each group the details regarding helmet NIV (number of hours used, highest pressure support level, and PEEP). Throughout the first 28 days, we will document the number of days with helmet treatment (> 1 h) and the total hours of helmet NIV. Non-tolerance to helmet NIV is defined as the need to remove the helmet because of patient preference or evidence of clinical deterioration. We will document other reasons for discontinuation of the helmet NIV (clinical improvement, the need for intubation, helmet removal due to change in goals of care or death while on helmet). We will document respiratory support after discontinuation of helmet NIV (mask NIV, HFNO, other oxygen devices, intubation). Violations to the study protocol will be documented including the use of NIV helmet in the usual care group and lack of attempt to use helmet NIV in the intervention group (Supplement Table S2).

#### Co-interventions

In both groups, we will document the use of other respiratory support modalities during the first 4 days (mask NIV with highest pressure support and PEEP, HFNO with flow rate, other oxygen devices, awake prone position), arterial blood gases, and fluid intake and output (Supplement Table S2).

#### Physiologic variables during the intervention

For the 28 days, we will document modalities of respiratory support, the use of sedation while not intubated (dexmedetomidine is permitted in the protocol), renal replacement therapy, and vasopressors/inotrope therapy. We will document the use of COVID-19 treatments, including corticosteroids, IL-6 receptor antagonists, and antiviral therapy. We will document serial arterial oxygen saturation (SaO_2_)/FiO_2_ ratio, fluid balance, and serial SOFA scores (Supplement Table S2).

#### Primary outcome

The primary outcome is all-cause 28-day mortality. The primary outcome tests the primary hypothesis that helmet NIV reduces 28-day mortality (Supplement Table S3).

#### Secondary outcomes

A detailed list of secondary outcomes with definitions has already been published and is outlined in Supplement Table S4. These secondary outcomes can be grouped as follows:
Mortality outcomes
ICU mortalityHospital mortalityEndotracheal intubation. We will document time to intubation, reasons for intubation as determined by the treating team (neurologic deterioration that is not attributed to sedation, persistent or worsening respiratory failure of NIV such as SaO2 < 88%, respiratory rate > 36/min, PaO_2_:FiO_2_ ratio < 100 or persistent requirement of FiO_2_ ≥ 70%, intolerance of mask or helmet NIV, airway bleeding, copious respiratory secretions, respiratory acidosis with pH < 7.25, hemodynamic instability, or significant radiological worsening). We will document mechanical ventilation parameters in the first 24 h after intubation (peak airway pressure, plateau pressure, PEEP in cm H_2_O), FiO_2_, tidal volume, and respiratory rate. We will also document oxygen rescue therapies during invasive mechanical ventilation (neuromuscular blocker infusion, recruitment maneuvers, inhaled nitric oxide, prone positioning, extracorporeal membrane oxygenation (ECMO)). We will report the percentage of patients who underwent tracheostomy.Continuous outcomes
ICU-free days at day 28Hospital length of stay (LOS)Invasive mechanical ventilation-free days at day 28Renal replacement therapy-free days at day 28Vasopressor-free days at day 28Safety outcomes
Skin injury at the nose, face, neck, and axillae, with the highest stage during the intervention period. We will use the stages as per the National Pressure Ulcer Advisory Panel [14]: stage I: non-blanchable erythema, stage II: partial thickness, stage III: full-thickness skin loss, and stage IV: full-thickness tissue lossBarotrauma, including pneumothorax, mediastinal air or subcutaneous emphysemaCardiovascular eventsDevice complications (such as helmet deflation or malfunction)Serious adverse events (SAEs)Follow-up study: There will be a follow-up of enrolled patients at day 180 about vital status, functional status (EuroQoL (EQ)-5D-5L), by an unblinded assessor, which is planned to be reported separately. For patients who have been discharged from the hospital before day 180, follow-up will be conducted by telephone.

We will also report protocol violations (Supplement Table S6).

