### Statistical analysis

Details of sample size calculation have already been published in the study protocol [11]. The sample size of 320 provides a power of 80% to detect a 15% absolute risk reduction in 28-day mortality from 40 to 25%. Categorical variables will be reported as numbers and frequencies and will be compared between the study groups using the chi-square test or Fisher’s exact test. Continuous variables will be reported as means and standard deviations or medians and the first and third quartiles (Q1–Q3) and will be compared between the study groups using the Student’s *t*-test or the Wilcoxon–Mann–Whitney test, as judged appropriate by normality testing using Shapiro–Wilk test. For serial measurements (such as SaO_2_:FiO2 ratio, fluid balance, and serial SOFA), we will test the change over time and the difference between the two study groups over time using generalized linear mixed effect models by considering the link function of logit to incorporate the binary nature of the response variable and link function of log for score outcomes, with no imputation for missing values. To adjust for multiple testing for secondary outcomes and subgroup analyses, we will use the false discovery rate (FDR) as described by Benjamini and Hochberg [15]. We will report associations as relative risk (RR) or hazard ratio (HR) with 95% confidence intervals (CI) or beta coefficient and 95% CI as appropriate. We will compare dyspnea scores and device discomfort scores using generalized linear mixed models, incorporating fixed effects of treatment, time, and the treatment by time interaction and random effects of patient and center. Tests will be two-sided and at the 5% significance level. All statistical analyses will be conducted using the SAS software version 9.4 (SAS Institute, Cary, NC, USA). The statistical analysis remains blinded to the research team until completion of primary outcome data on the study population and will be performed by the study biostatistician. A summary of the analysis plan is provided in Table 1.

**Table 1 Tab1:** Summary of the analysis plan

Variables	Intention-to-treat cohort	Per-protocol cohort
Baseline characteristics	No statistical comparisons	None
Intervention and co-interventions	Chi-square, Fisher’s exact test, Wilcoxon–Mann–Whitney test, *t*-test as applicable	None

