#### Analysis of secondary outcomes

Secondary outcomes will be compared in the intention-to-treat cohort only. Categorical outcomes will be compared in the intention-to-treat using a chi-square test. Results will be reported as RR with 95% CI. Continuous outcomes will be compared using generalized linear mixed models. Results will be reported as beta estimates with 95% CI.

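### Ventilator settings and rescue therapies that exist only after intubation fall under a blanket between-arm testing rule, and time to intubation has no assigned time-to-event analysis

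*SAP article*

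**What the plan says.** In the SAP article, Secondary outcomes, the outcome of endotracheal intubation carries three kinds of supporting data:

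- Timing and reasons: "We will document time to intubation, reasons for intubation as determined by the treating team".
- Ventilator settings: "We will document mechanical ventilation parameters in the first 24 h after intubation". The list covers peak and plateau pressure, PEEP, FiO2, tidal volume and respiratory rate.
- Rescue therapies for oxygenation during invasive ventilation, such as neuromuscular blockade, proning and ECMO.

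The testing rules stand elsewhere:

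- Statistical analysis, categorical data: "Categorical variables will be reported as numbers and frequencies and will be compared between the study groups", by chi-square or Fisher's exact test.
- Statistical analysis, continuous data: these "will be compared between the study groups using the Student’s *t*-test or the Wilcoxon–Mann–Whitney test".
- Analysis of secondary outcomes: "Secondary outcomes will be compared in the intention-to-treat cohort only". On method: "Continuous outcomes will be compared using generalized linear mixed models".
- Table 1: the entry "No statistical comparisons" appears once, in the row for baseline characteristics.

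Cox and Kaplan–Meier methods are assigned only to the primary outcome. Statistical analysis allows a hazard ratio where appropriate, without linking it to intubation. No section names intubated patients as a denominator or labels any of these items descriptive.

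**The concern.** A patient who is never intubated has no plateau pressure on the ventilator and no rescue therapy during invasive ventilation. Any between-arm test of these items therefore uses only patients who were intubated, and intubation occurs after randomisation. The article itself expects the helmet to change it: the Background cites an intubation risk ratio of 0.26 against standard oxygen, and a trial against high-flow oxygen with significantly fewer intubations. Those comparators differ from this trial's usual care, but the expected direction is clear.

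If the helmet averts the milder patients' intubations, the helmet patients who are still intubated are sicker on average and may show worse settings. If it averts the sickest patients' intubations, the reverse happens. Neither is an effect of the helmet on the settings. In an unblinded trial, such a difference with a p-value could be read as a randomised finding of harm or benefit.

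Time to intubation can be analysed properly in everyone randomised, but the plan does not assign such an analysis. The rules for continuous data are what remains, and they would permit a comparison of intubated patients alone.

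**Working it through.** **The plan's own figure.** The only design figure is 80% power for mortality of 40% v 25% with 160 per arm. By the normal approximation, z = (0.15 × √160 − 1.96 × √(2 × 0.325 × 0.675)) / √(0.40 × 0.60 + 0.25 × 0.75) = (1.897 − 1.298) / 0.654 = 0.916, so power is 82.0% (81.6% at the final level of 0.048). This agrees closely enough with 80%. The present point does not depend on it.

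**Does documenting an item mean it is not tested?** No. Co-interventions are also introduced as items to be documented, and Table 1 tests them. Serial oxygenation, fluid balance and SOFA are introduced the same way, and Statistical analysis tests them over time. Where no test was wanted in the intention-to-treat cohort, Table 1 says so, and it does so for baseline characteristics only.

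**Size of the selection effect.** From the article: 160 per arm, two-sided 5%. Assumed, because the article gives no such figures: 50% intubated in usual care; 40% or 30% with helmet; standard normal severity u, with intubation above a threshold; a ventilator variable with SD 1 in the whole cohort and correlation ρ = 0.5 with u; no helmet effect on that variable. About 80 patients (160 × 0.50) contribute in usual care, and 64 (160 × 0.40) or 48 (160 × 0.30) with helmet.

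Expected false difference = ρ × [E(u | intubated, helmet) − E(u | intubated, usual care)].

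- Usual care, upper 50%: E(u) = 0.3989 / 0.50 = 0.798.
- Helmet 40%, mildest averted: 0.3863 / 0.40 = 0.966. Difference 0.5 × (0.966 − 0.798) = +0.08 SD.
- Helmet 30%, mildest averted: 0.3477 / 0.30 = 1.159. Difference 0.5 × (1.159 − 0.798) = +0.18 SD.
- Helmet 40%, sickest averted: (0.3989 − 0.1755) / 0.40 = 0.559. Difference 0.5 × (0.559 − 0.798) = −0.12 SD.
- Helmet 30%, sickest averted: (0.3989 − 0.2800) / 0.30 = 0.397. Difference 0.5 × (0.397 − 0.798) = −0.20 SD.

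Simulation of the same set-up (4,000 trials per row, t-test in intubated patients only):

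| Helmet intubation | Averted cases | Mean false difference | p < 0.05 |
|---|---|---|---|
| 40% | mildest | +0.08 SD | 8.0% |
| 40% | unrelated to severity | about 0 | 4.9% |
| 40% | sickest | −0.12 SD | 11.5% |
| 30% | mildest | +0.18 SD | 18.6% |
| 30% | unrelated to severity | about 0 | 5.2% |
| 30% | sickest | −0.21 SD | 23.2% |

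The simulated shifts match the formula to within about 0.01 SD. With equal intubation rates (50% v 50%) the rejection rate is also about 5%.

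**Time to intubation.** Assume in addition that sicker patients are intubated earlier. With 50% v 30% intubated, the mildest averted and correlations of 0.3 to 0.7, an intubated-only Wilcoxon test gives helmet-to-usual-care median ratios of 0.90 down to 0.77 and rejects in 8% to 39% of trials (1,500 trials each). This shows what the unassigned analysis could produce, not what the plan commits to.

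**The case against.** No sentence attaches a test to ventilator settings, rescue therapies or time to intubation. The separate list of continuous secondary outcomes (ICU-free days, length of stay, organ-support-free days) omits them, so they read as supporting data to a yes/no outcome. If they were continuous secondary outcomes, they would go to mixed models, not to a t-test or Wilcoxon test. If they are only variables under the general rule, the provisions for secondary outcomes do not attach. Outcome definitions are referred to the published protocol and Supplement Table S4, which are not shown.

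Most of this stands, and it rules out three stronger readings that a reader might infer:

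- That the plan expressly prescribes a t-test or Wilcoxon test in intubated patients. It does not; the comparison follows from the general rule and the single exemption in Table 1.
- That false signals would enter the false discovery rate family. That adjustment is for secondary outcomes and subgroups, and whether these items belong is unclear.
- That time to intubation exists only for intubated patients and will be compared invalidly. It can be analysed in all randomised patients with censoring, and the general allowance for hazard ratios leaves room for that. The fault is that no such analysis is assigned.

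The size is also open. It rests on assumed rates and correlations, and it vanishes if averted intubations are unrelated to severity. An intervention that selectively averts early intubations arguably does affect timing, so large rejection rates for time under that scenario are not plainly false positives.

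What the objection does not remove is the breadth of the general rule. A mixed model would not help, since it too can use only patients with a value.

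**Conclusion.** The point holds in limited form. Read consistently, the plan's rules would test post-intubation ventilator settings and rescue therapies between arms in a subset formed after randomisation, and they leave time to intubation open to the same treatment. Under the stated assumptions (50% v 40% to 30% intubated, correlation 0.5, averted cases at one end of the severity range), the false-positive rate for a ventilator setting is about 8% to 23% against a nominal 5%, in either direction. It is about 5% if averted cases are unrelated to severity. The documents cannot narrow that range.

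Only supporting variables are affected. Mortality at 28 days and the relative risk of intubation use all randomised patients and are untouched. It should be corrected before the data are analysed, but it does not threaten the trial's main conclusion.

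**What to change.** Add two statements to the SAP:

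1. Ventilator settings after intubation and rescue therapies during invasive ventilation are described among intubated patients, with the number contributing in each arm, without between-arm p-values and outside any false discovery rate family.
2. Time to intubation is analysed in all randomised patients over 28 days, by cumulative incidence or cause-specific hazard with death as a competing event, and not by a t-test, Wilcoxon test or mixed model in intubated patients only.

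The cost is two sentences and one further analysis of data already being collected. The p-values on the ventilator settings and rescue therapies are given up.
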